#### Biologic sample collections and storage during clinic visits

This study collects both saliva and blood. Both child and parent (caregiver) provide saliva for the detection of cortisol levels. Saliva collections occur before and after each intervention or attention control session at all 4 sessions for standard risk participants and the first 4 sessions for high-risk participants. The saliva is collected in a Salimetrics SalivaBio Oral Swab or SalivaBio Children’s Swab for the caregiver and child, respectively. The swab is immediately placed in the prelabeled storage tube, placed on dry ice post-collection, and stored at -80 C.

Blood is only collected from the children. At each site, 5 mL of blood is collected as part of routine study draws the morning of their sessions and used to isolate serum for cytokine analysis. This occurs at sessions 1 and 4 for all children with an additional draw at session 8 for high-risk children. Our primary site collects an additional 1 mL of blood to conduct a blood cortisol analysis for the purpose of monitoring adrenal function in a subset of the children on study. These collections occur at the child’s end of induction clinic appointment as well as sessions 1 through 4. Serum for cytokine analyses will be held until the end of the study at which point multiplexed analyses will be run. Serum for monitoring adrenal function in the children will be run on a yearly basis.

Treating physicians, at our three hospitals, have assigned clinic days and times (morning vs. afternoon). This will minimize variability in the timing of saliva collection between appointments. We will track day/time of collections and other factors that may contribute to child and parent cortisol interpretation (i.e., sleep, food/drink intake, medications).

#### Data collection on parent/child medications

We created a survey to identify and monitor sleep, food, and medication intake that may interfere with our ability to interpret cortisol collections. This survey is administered at the same time as our baseline participant questionnaires prior to any study sessions. The survey is structured in our database such that after parents fill out medication information for themselves and their children, they only need to update any changes that have occurred each visit for which there is a biologics collection. This process saves participants time and ensures smoother clinic flow.

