#### Preliminary analyses

Prior to hypothesis testing, we will calculate coefficient alpha as a measure of internal consistency reliability on all multiple-item scales. Construct validity will be assessed by calculating Pearson or Spearman correlations among scales to determine if correlations are in the expected direction. We will present descriptive statistics for the AME group and the attention control group with respect to demographic and baseline outcome variables. We will control for child and parent age, site, risk level (standard or high), greater distress with prior hospitalizations, greater traumatic stress symptoms, time of collection of pre-session cortisol, and child and parent sex in all models. Age, site, and risk level are stratification variables. Time of collection of pre-session cortisol will account for differences based on standard diurnal differences. Although time of collection will be similar within each child, there will likely be between-child differences in time of collection (e.g., some children will have collections in morning and some in afternoon) that we will control for in analyses.

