#### Main analyses

For analyses below, we will analyze as randomized and attempt to collect outcome data on non-completers, following the intent-to-treat principle. For Aims 1 and 2, each outcome will be modeled separately, and we will examine sex as a biological variable by including sex as a covariate to control for its relationship with the outcomes and the interaction of sex and intervention group to examine if there are differential effects by intervention group. For Aim 1 (H1.1 and H1.2), the outcome will be the pre- to post- percent change in cortisol for each session. A linear mixed model will be fit with the independent fixed effects variables of intervention and session (1 to 4). Subject will be a random effect. We will use an F-test to test the intervention effect. For Aim 2 (H2.1, 2.2, 2.3), our primary goal is to test mediation effects. Mediation effects will be estimated in an ANCOVA setting, fitting the appropriate mediation models using MPlus [66] and then testing indirect effects using the percentile bootstrap approach to estimate the indirect effect [55]. The mediation model with two-path mediation effects specifies that the intervention will act through the mediator on the outcome and also have a direct effect on the outcome. Each outcome model will have 3 key predictors (intervention, two proximal mediators), and control for T1 outcome and covariates described above. For testing cortisol as a mediator, we will use (1) the estimated average percent change estimated from the mixed model, and (2) the % change from pre-session 1 to post session 4. In addition, we will look at child and parent cortisol levels both separately and together (multiple mediation model) in order to fully assess if/how they function together as mediators. Thus, for any single outcome, up to 6 models will be examined. For all mediation models in Aim 2, we will assess goodness-of-fit (GOF) using standard GOF measures (comparative fit index, root mean square error of approximation, and root mean square residual). For Aim 3, an exploratory aim, we will use graphical plots and non-linear repeated measures models to model the trend in percent changes in cortisol within and between intervention groups across the 4 sessions for all participants and across 8 sessions for high risk participants.

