To further address concerns about possible adrenal insufficiency at the start of consolidation, we will examine blood cortisol levels in a sub-sample of study participants (Indianapolis site) at the end of induction therapy, and on days during consolidation therapy when participants are scheduled to receive study sessions 1–4. This will allow us to identify participants in the sub-sample with adrenal insufficiency at the start of consolidation, which will enable us to better interpret alterations in salivary cortisol levels over time in those individuals. It may also allow us to recognize patterns in salivary cortisol levels that would indicate adrenal insufficiency to identify and control for participants at other sites with this same issue. The addition of the child blood cortisol collections will increase study rigor and interpretation of child salivary cortisol.

The *second challenge* was to select appropriate timing for cortisol collection while identifying strategies to avoid burdening children and parents [18, 19]. Cancer treatments’ interference with sleep schedules can disrupt diurnal rhythms of cortisol production [74]. To address these challenges, we will examine more immediate changes in cortisol that occur around the time of the AME or attention control experience (pre/post-session) and over time (across 4 weekly sessions); an approach taken in three previous pediatric studies [75–77]. This also mitigates the potential for increased burden on parents associated with collecting, storing, and transporting multiple samples from home to clinic, and related concern about sample viability. Over time, we expect that the size of within-child percent decrease in cortisol among AME children will become larger than the corresponding decrease observed in attention control children. Focusing on relative levels of cortisol within children minimizes the influence of children’s absolute levels of cortisol, for which the diurnal rhythms may be altered. With regard to timing, treating physicians at our three hospitals have assigned clinic days and times (morning vs. afternoon), and this will help minimize variability in the timing of salivary cortisol collection between appointments (e.g., patient A is always in clinic in the morning, patient B is always in clinic in the afternoon). In addition, we will statistically control for timing of cortisol collection as necessary.

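### Sleep is surveyed before any session as a factor that may disturb cortisol, but the covariates fixed for all models omit it, so the Aim 2 cortisol-to-outcome path stays open to confounding by baseline sleep

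*Protocol article*

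**What the plan says.** Three places in the protocol article tie sleep to cortisol.

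- The section Data collection on parent/child medications gives the purpose of the survey: "We created a survey to identify and monitor sleep, food, and medication intake that may interfere with our ability to interpret cortisol collections". On timing: "This survey is administered at the same time as our baseline participant questionnaires prior to any study sessions". A sleep value unaffected by AME should therefore exist for each dyad.
- Biologic sample collections and storage during clinic visits: the team will track "other factors that may contribute to child and parent cortisol interpretation (i.e., sleep, food/drink intake, medications".
- Discussion of biomarker strategy, second challenge: cancer treatment's "interference with sleep schedules can disrupt diurnal rhythms of cortisol production".

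The adjustment set is fixed elsewhere. Preliminary analyses states: "We will control for child and parent age, site, risk level (standard or high), greater distress with prior hospitalizations, greater traumatic stress symptoms". The list then goes on to its last items, with its scope: "time of collection of pre-session cortisol, and child and parent sex in all models". Main analyses says each Aim 2 outcome model will "control for T1 outcome and covariates described above". Sleep is in neither place. Food and drink intake and medication, which are recorded for the same reason, are also absent.

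The mediator is defined in two ways: "the estimated average percent change estimated from the mixed model", and the percentage change from before session 1 to after session 4.

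**The concern.** Sample size and power analysis calls mediation the primary goal and sizes the trial on it. The indirect effect is the product of two paths. The first, AME to cortisol, is randomised. The second, cortisol to outcome, is an observational association within arms. A common cause of cortisol change and of the outcome biases it. Sleep is a plausible common cause of cortisol change and of mood, quality of life or cytokines. The protocol itself supplies the link to cortisol and records sleep before treatment.

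Clock time of the pre-session sample does not stand in for sleep. The article uses it to correct for the ordinary diurnal pattern, and also says disturbed sleep can disrupt that pattern.

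At stake is an indirect effect declared because poor sleepers have both a different cortisol change and worse outcomes, with no effect of cortisol on the outcome. In Aim 1 the omission costs only precision.

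**Working it through.** **Inputs.** From Sample size and power analysis: 170 dyads retained (85 per group); AME to mediator 13% of variation, mediator to outcome 7%, AME to outcome 2%; stated power 88% (Sobel) and 90% (t-test, medium effect). From Main analyses: percentile bootstrap, T1 outcome in the model. Assumed, because the article gives no values: the effects of sleep on cortisol change, on the T1 outcome and on the T2 outcome, and the T1-to-T2 coefficient h.

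**1. The plan's own figures.** With standardised coefficients √0.13, √0.07 and √0.02, a simulated Sobel test at n = 170 gives 88.2% power against 88% stated. A t-test with 85 per group and d = 0.5 gives 90.0% against 90%. Dropout: 170/0.75 = 226.7, so 227 against 228. No design figure is in dispute. The planned indirect effect is √(0.13 × 0.07) = 0.095.

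**2. Bias formula.** Let sleep have standardised effect m on cortisol change, t on the T1 outcome and a direct effect d on the T2 outcome beyond T1. Let cortisol have no effect on the outcome. With sleep omitted and T1 adjusted, the apparent cortisol-to-outcome coefficient is

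b = d × m(1 − t²) / (0.87 − m²t²),

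where 0.87 = 1 − 0.13. The false indirect effect is √0.13 × b. For m = t = d = 0.3: b = 0.3 × 0.273/0.8619 = 0.095, and the false indirect effect is 0.361 × 0.095 = 0.034.

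**3. Percentile-bootstrap simulation** (n = 170, 400 resamples, 1,000 trials per row, h = 0.5, true b = 0, nominal 5%):

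| m / t / d | Indirect effect, formula | Indirect effect, simulated | Rejection, sleep omitted | Rejection, sleep added |
|---|---|---|---|---|
| 0 / 0 / 0 | 0 | −0.0003 | 5.7% | 5.5% |
| 0.1 / 0.1 / 0.1 | 0.004 | 0.003 | 5.7% | 5.4% |
| 0.2 / 0.2 / 0.2 | 0.016 | 0.016 | 10.9% | 4.3% |
| 0.3 / 0.3 / 0.3 | 0.034 | 0.036 | 32.6% | 5.0% |
| 0.3 / 0 / 0.3 | 0.037 | 0.037 | 30.5% | 5.9% |
| 0.3 / 0.3 / 0.1 | 0.011 | 0.012 | 9.3% | 5.4% |

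The simulation standard error at 5% is √(0.05 × 0.95/1000) = 0.7 percentage points, so the last column is compatible with 5% throughout. If AME does not move cortisol, the rate is 1.2% even with all sleep effects at 0.3.

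**4. Sleep equally correlated with the T1 and T2 outcome.** This is the more natural case for a baseline trait. If sleep correlates r with both, then r = h·r + d, so d = r(1 − h): adjusting for T1 removes much of the sleep effect. Joint-significance test at 0.05, h from 0.5 to 0.7:

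| Correlation with cortisol / outcome | d at h = 0.5; 0.7 | Without T1 | With T1, as planned |
|---|---|---|---|
| 0.2 / 0.2 | 0.10; 0.06 | 8% | 6–7% |
| 0.2 / 0.3 | 0.15; 0.09 | 12% | 6–7% |
| 0.3 / 0.3 | 0.15; 0.09 | 22% | 8–9% |
| 0.3 / 0.4 | 0.20; 0.12 | 35% | 9–13% |

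The last column describes the planned model. The column without T1 does not.

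**5. Limits.** The simulations use one mediator and leave out the other planned covariates. Prior-hospitalisation distress and traumatic stress symptoms may absorb part of any sleep effect. The return to about 5% assumes sleep is measured without error. At reliability 0.5, in a model without T1, the rate stays at about 8–9% (0.3/0.3) and 12–13% (0.3/0.4).

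**The case against.** The strongest reply is that the protocol answers the sleep problem in the same paragraph that raises it. It studies short-term, within-child relative change, so that absolute level and a disturbed rhythm matter less. That stands in part: a pre-to-post-session percentage change is less exposed to baseline sleep than a level would be, and correlations of 0.2–0.3 may be generous. It protects least for the second mediator, from before session 1 to after session 4, which spans weeks.

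The second reply is that T1 adjustment removes most of the effect. It does remove much of it. A reader might infer false-mediation rates of 22% or 35% from a model without T1, but the plan does not fit that model.

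Third, the analysis plan is not shown, and the article says these factors are tracked for interpretation. A reader might infer that the survey data will never be analysed. The article does not say so; it only states no analytic use. But it does give an explicit covariate list for all models, so the omission of sleep is more than a detail left for later.

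Fourth, a reader might extend the point to food and drink as confounders of Aim 2, or assume a time since last meal is available. The article does not support this. The second-challenge discussion mentions sleep, not food; no such time variable is described; and visit-by-visit updating is spelled out only for medication.

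**Conclusion.** The point holds as a recommended change. A factor the protocol names as disturbing cortisol, and surveys before any session, is missing from the covariates fixed for all models, and the primary mediation aim needs control of exactly this kind of variable.

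The size is modest under most assumptions. The false-mediation rate is about 6–7% at a sleep correlation of 0.2 with cortisol change, and about 8–13% at 0.3 with cortisol and 0.3–0.4 with the outcome. If sleep also acts directly on the T2 outcome beyond T1, it is about 11% at effects of 0.2 and 31–33% at 0.3. In that last case the spurious indirect effect is about 0.036/0.095 = 38% of the planned one. The inflation is negligible at 0.1 and absent if AME does not change cortisol. All of this rests on assumed sleep effects.

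A reader might infer that Aim 1 is biased too. It is not, because that comparison is randomised.

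**What to change.** Add to the covariate list under Preliminary analyses the sleep value surveyed before session 1: the child's or the parent's, matching the cortisol in the model, and both where both mediators are fitted together. Use it in the Aim 2 mediator and outcome models, and in Aim 1 for precision.

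Keep sleep from later visits, if it is recorded, for sensitivity analysis only. AME, including its encouraged use between visits, could change later sleep, and adjusting for it could remove part of the effect under study.

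Use food and drink intake only as a session-level covariate in the Aim 1 cortisol model, in whatever form the survey records it.

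The cost is a wording change and one or two degrees of freedom out of 170, with some missing survey items to handle. Residual confounding will remain if sleep is measured with error, so the adjusted indirect effect should still be read with that caution.

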#### Masking process

During study introduction and informed consent, the AME and ASB conditions are presented as equal conditions that inform our understanding about the use of play experiences, like music and stories, to reduce child and parent stress during cancer treatment. As such, child/parent dyads are masked to whether they are receiving the intervention or attention control condition. Data collectors administering baseline (T1) and post-intervention (T2) questionnaires are masked to participants’ group assignment. Should a data collector who is responsible for T2 data collection become aware of a participant’s group assignment, we assign another data collector unaware of group assignment to administer measures. Data collectors administering pre- and post-session saliva collections will not be masked to group assignment due to timing/proximity of collections to session delivery.

### Data analysis

#### Analysis of biomarkers

Saliva samples cortisol levels will be analyzed using manufacturer validated R&D® ELISA kits and controls. The levels of IL-1$$\beta$$, IL-6, TNF-$$\alpha$$, IFN-$$\gamma$$, IL-4, IL-10, and IL-13 in patient serum will be analyzed using a Bio-Rad multiplex immunoassay 7-plex kit and controls in the Multiplex Analysis Core. Reproducibility of these kits is validated by the manufacturer and each plate will be run with appropriate standards as well as internal controls to ensure reliability across lots. Kit lot numbers as well as certificates of analysis (provided by the manufacturer) will be kept with the study records.

#### Preliminary analyses

Prior to hypothesis testing, we will calculate coefficient alpha as a measure of internal consistency reliability on all multiple-item scales. Construct validity will be assessed by calculating Pearson or Spearman correlations among scales to determine if correlations are in the expected direction. We will present descriptive statistics for the AME group and the attention control group with respect to demographic and baseline outcome variables. We will control for child and parent age, site, risk level (standard or high), greater distress with prior hospitalizations, greater traumatic stress symptoms, time of collection of pre-session cortisol, and child and parent sex in all models. Age, site, and risk level are stratification variables. Time of collection of pre-session cortisol will account for differences based on standard diurnal differences. Although time of collection will be similar within each child, there will likely be between-child differences in time of collection (e.g., some children will have collections in morning and some in afternoon) that we will control for in analyses.

#### Missing data and multiple comparisons

We will compare all baseline variables between subjects who drop out of the study and those who do not using two-sample *t* tests, chi-square tests, or non-parametric equivalents as appropriate. MPlus software will incorporate participants who drop out before completion by using the MPLUS imputation method to perform a bias adjustment for missing data under maximum likelihood estimation and the assumption that data are missing at random. If we find that missing data are not missing at random, we will use a pattern mixture modeling approach to address; note we expect up to 25% attrition but minimal missing data on instruments (< 1%). We will adjust *p* value for multiple comparisons using the Bonferroni method for parent emotional/traumatic distress as there are two outcomes for this domain. For cytokine analyses, there are 7 cytokines of interest, so a Hochberg step-up approach will be used for these analyses.

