### Sample size and power analysis

We will recruit a total sample size of 228 child/parent dyads and assume 25% attrition to retain 170 child/parent dyads (85 dyads/group) at Time 2. The primary goal of this study is to examine mechanisms via the mediation effects of the AME intervention. We will use the percentile bootstrap method to estimate the indirect/mediated effect [55]. The sample size needed for this study is primarily driven by the power needed for the mediation hypothesis in Aim 2. Simulations of the two-path mediation model in Mplus [56] show that 170 subjects are needed to have 88% power to test the total indirect effect using the Sobel approach when the effect of the independent variable (AME in this case) on the mediator is at least medium (13% of variation explained), mediator on the outcome is between small and medium (7% of variation explained), and independent variable on the outcome is small (2% of variation explained). Via simulation, the Type I error with this sample size under a model that assumes no indirect effect is also less than 0.007, which will readily accommodate the multiple comparison adjustments planned below (e.g. with 7 cytokines a conservative Bonferroni adjustment would be 0.05/7 = 0.007). A sample size of 170 will also afford 90% power to detect a medium effect size for H1.1 and H1.2 based on a two-sample t-test with a two-sided alpha level of 0.05. Fitting models that allow for repeated measures across session will result in improved power. Using the percentile bootstrap method instead of Sobel should afford the same or greater power.

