**Parent Outcomes**					
Parent Emotional and Traumatic Stress Symptoms	Profile of Mood States-Short Form (POMS)[63] Impact of Events Scale-Revised (IES-R)[64]	37 22	0.99** 0.84-0.91†	T1,T2 T1, T2	Parent Parent
Parent Quality of Life	Index of Well-being[65]	9	0.93†	T1, T2	Parent

†Cronbach’s alpha; **correlation with POMS

*Blood taken during scheduled draw

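### Plain Bonferroni for the two parent-distress scales is valid but gives up a little power that Holm or Hochberg would recover at the same family-wise error

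*Protocol article*

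**What the plan says.** Under 'Missing data and multiple comparisons', the Protocol article adjusts p-values "using the Bonferroni method for parent emotional/traumatic distress as there are two outcomes for this domain". Table 2 lists POMS Short Form and IES-R as the measures of parent emotional and traumatic stress symptoms, so these are the two outcomes.

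The next sentence treats the other multi-outcome domain differently: "there are 7 cytokines of interest, so a Hochberg step-up approach will be used for these analyses". No reason is given for the two methods.

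The parent scales belong to Hypothesis 2.3. 'Sample size and power analysis' calls mediation the primary goal and says Aim 2 drives the sample size: "170 subjects are needed to have 88% power to test the total indirect effect using the Sobel approach". That figure assumes 13%, 7% and 2% of variation explained for AME on mediator, mediator on outcome and AME on outcome. No significance level is attached to the 88%, and no power is given at 0.025. The section adds that the percentile bootstrap, which is the test planned under 'Main analyses', should have power at least equal to Sobel's.

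**The concern.** With two tests, Bonferroni is dominated as a decision rule. Holm starts at the same 0.025 and, once one scale passes, tests the other at 0.05. It needs no assumption about dependence. Hochberg rejects both when the larger p-value is at most 0.05. It needs independence or positive dependence, which is plausible for two distress scales that share the same AME-to-cortisol path. Neither can reject less than Bonferroni.

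At stake is power for Hypothesis 2.3. That hypothesis names both emotional and traumatic distress, so the case in which both scales are mediated is the one the investigators expect. It is also the case in which a step-wise rule gains most. The sample size section does not settle the matter: a simulated Type I error below 0.007 shows that the test is conservative under no effect, but says nothing about power at a stricter threshold.

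**Working it through.** **Inputs from the document.** N = 170 (85 per group); variance explained 13%, 7%, 2%; two outcomes; percentile bootstrap as the planned test, Sobel as the planning test.

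**Assumptions.** Two-sided 0.05 for Aim 2 (stated only for Aim 1: "90% power to detect a medium effect size for H1.1 and H1.2 based on a two-sample t-test with a two-sided alpha level of 0.05"); one mediator; no covariates; residual correlation between the scales, which the document does not give, varied from 0 to 0.7.

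**Model.** AME coded ±1. M = aX + error and Y = bM + c′X + error, with a = √0.13 = 0.361, b = √0.07 = 0.265, c′ = √0.02 = 0.141. Residual variance of Y = 1 − (b² + c′² + 2abc′) = 1 − (0.07 + 0.02 + 0.027) = 0.883. Both scales share M.

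**Step 1: reproduce the plan's figures.** Sobel z = âb̂ / √(â²s_b² + b̂²s_a²), two-sided 0.05, gives 88.2% to 88.5% (stated 88%). A t-test with d = 0.5 and 85 per group gives 90.0% (stated 90%). Both reproduce.

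**Step 2: decision rules for two p-values.**
- Bonferroni: reject a scale if p ≤ 0.025.
- Holm: as Bonferroni; also reject the other scale if the smaller p ≤ 0.025 and the larger p ≤ 0.05.
- Hochberg: as Bonferroni; also reject both if the larger p ≤ 0.05.

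**Step 3: planned percentile bootstrap, both effects real** (1,500 trials, 1,000 resamples).

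| Residual correlation | Unadjusted | Bonferroni | Holm | Hochberg |
|---|---|---|---|---|
| 0.3, per scale | 92.2% | 87.2% | 91.2% | 91.7% |
| 0.6, per scale | 91.1% | 85.4% | 88.9% | 89.8% |
| 0.3, both scales | – | 77.5% | 85.4% | 85.9% |
| 0.6, both scales | – | 77.4% | 84.4% | 85.3% |

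Cost of Bonferroni per scale: 92.2 − 87.2 = 5.0 and 91.1 − 85.4 = 5.7 points. Recovered by Holm: 4.0 and 3.5. Recovered by Hochberg: 4.5 and 4.4. Gain in supporting both scales: 7.0 to 8.4 points. A second set (2,000 trials; correlations 0.3, 0.5, 0.7) gave both-scale support of 75%, 80%, 79% with Bonferroni, 84%, 88%, 87% with Holm and 84%, 88%, 88% with Hochberg, a gain of 8 to 9 points. The unadjusted per-scale power should not depend on the correlation, so the difference between 92.2% and 91.1% shows the simulation error, about one point. The rules are compared on the same simulated trials, so the differences between them are steadier.

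**Step 4: Sobel, for comparison** (40,000 trials, correlation 0 to 0.7). Per scale: 88% unadjusted, 78.6% to 78.9% Bonferroni, 84.0% to 85.7% Holm, 86.2% to 86.9% Hochberg. Bonferroni costs 9 to 10 points; Holm returns 5 to 7 and Hochberg 7 to 8.

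**Step 5: only one effect real** (Sobel). Bonferroni 78.3% to 78.6%, Hochberg 78.6% to 78.9%: a gain of 0.2 to 0.3 points. Holm cannot gain more than Hochberg.

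**Step 6: error control.** For two independent true nulls, Hochberg's family-wise error is 1 − 0.975² + 0.025² = 0.0494 + 0.0006 = 0.050. With normal test statistics correlated from −0.9 to 0.9, Bonferroni and Holm gave 3.6% to 5.0% and Hochberg 4.1% to 5.0%. With the bootstrap, no cortisol-to-outcome effect and correlation 0.5, the figures were 4.8% for Bonferroni and Holm and 5.0% for Hochberg.

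**The case against.** The strongest reply is that nothing here is an error. Bonferroni over two outcomes is pre-specified, tied to a named family and valid. Using a simple rule for two tests and a step-up rule for seven is not a contradiction, since Bonferroni's conservatism grows with the number of tests. That stands: a reader might infer from the adjacent sentences that the plan is inconsistent, but the text does not show this.

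A reader might also infer that about 10 points of power are at stake. That figure compares Bonferroni with no adjustment, which nobody proposes, and uses the Sobel test, which is not the planned analysis. Under the bootstrap, Bonferroni still leaves about 85% to 87% per scale, close to the stated 88%. Nor is Bonferroni's own loss largest when both scales respond: its threshold is 0.025 either way, and only the step-wise gain depends on the other scale.

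Finally, the change is not free. A bootstrap test is usually read from whether the interval excludes zero, and Bonferroni matches a 97.5% interval exactly. Under a step-wise rule, a scale with p between 0.025 and 0.05 can be declared significant while its 97.5% interval includes zero. Wanting test and interval to agree is a legitimate reason to keep Bonferroni.

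The simulation is also simpler than the plan, which allows up to six models per outcome, with child and parent cortisol separately and together, and adjusts for the baseline outcome and covariates. The figures are therefore illustrative. The ordering of the rules does not depend on the simulation.

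**Conclusion.** The point holds as a cheap efficiency improvement. It does not question the validity of the plan or the adequacy of the sample size. A step-wise test never rejects less than Bonferroni and holds the same 5% family-wise error: Holm always, Hochberg under independence or positive dependence. The benefit is modest and conditional: it needs both scales to be truly mediated and practically vanishes otherwise. The one-effect case was computed with Sobel only. Under the bootstrap it should be similarly small, because a gain needs the real effect to fall between 0.025 and 0.05 while the null scale happens to pass 0.05.

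**What to change.** In 'Missing data and multiple comparisons', replace Bonferroni for POMS and IES-R by one of:

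- **Holm**, if no dependence assumption is wanted: the scale with the smaller p-value is supported if p ≤ 0.025; if it is, the other is supported if its p ≤ 0.05.
- **Hochberg**, to match the cytokines: both scales are supported if the larger p ≤ 0.05; otherwise only a scale with p ≤ 0.025.

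Either rule can be read from 95% and 97.5% percentile intervals. State that decisions rest on the adjusted p-values and that the 97.5% intervals are descriptive, so that a disagreement between the two is not misread. If the team prefers exact agreement of test and interval, keep Bonferroni and say so in a clause.

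The cost is one sentence, made before any outcome data are seen by arm. It needs no extra patients, data or visits.
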